### Statistical Analyses

Statistical tests will be performed with SPSS Statistics (version 29; IBM Corp). Significance is defined as *P*<.05. Quantitative data are reported as means and SD. Statistical significance for quantitative variables is assessed using Student *t* test or 1-way ANOVA. Categorical data are presented as percentages, and significant differences are determined using chi-square tests.

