**Methods:**

This single-blind randomized controlled trial (ChiCTR2300068327) enrolled 80 adults with AS from the Chinese People’s Liberation Army (PLA) General Hospital. Participants were randomized 1:1 to: DFEP Group: 24-week sensor-guided exercises via the Healbone Mini Program (Jiakangzhongzhi, Co), with real-time feedback and remote physiotherapist oversight. Control Group: standard home-based exercises with written instructions. The primary outcome is the change in Ankylosing Spondylitis Disease Activity Score with C-reactive protein (ASDAS-CRP) at 24 weeks. Secondary outcomes include Bath Ankylosing Spondylitis Disease Activity Index (BASDAI), Bath Ankylosing Spondylitis Functional Index (BASFI), Bath Ankylosing Spondylitis Metrology Index (BASMI), Assessment of Spondyloarthritis International Society Health Index (ASAS HI), 36-Item Short Form Survey (SF-36), pain visual analog scale, Five-Times-Sit-to-Stand, 4-meter walk test, Hamilton Anxiety Scale (HAMA), Hamilton Depression Scale (HAMD), and adherence. Analyses will follow an intention-to-treat approach with the Last Observation Carried Forward for missing data; continuous variables will be compared with *t* tests or ANOVA, and categorical variables with chi-square tests, using a 2-sided =.05.

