### Participants

Patients diagnosed with AS according to the 1984 modified New York criteria [7] at the Chinese PLA General Hospital, either as a first-time diagnosis or previously, were enrolled in the study and assigned to 2 groups. In addition to collecting their demographic characteristics (age, gender, weight, height, and BMI), the patients were also questioned about occupation, main symptoms, time of diagnosis, and drug usage (nonsteroidal anti-inflammatory drug, disease-modifying antirheumatic drugs, including biologics). Other inclusion criteria were aged ≥18 years, stable drug treatment in the preceding month, and ASDAS-CRP between 1.3 and 3.5 [8]. Exclusion criteria were cardiovascular disease or clinical status at high risk, screened with the American Heart Association/ACSM Health/Fitness Facility Preparticipation Screening Questionnaire [9], cervical vertebra bridges, surgery within the preceding 6 months, regular exercise in the preceding 3 months (eg, yoga, Tai Chi, Baduanjin 3 or more times per week, 20 minutes per time), and factors leading to the inability to receive regular exercise rehabilitation (such as language impairment, difficulty in understanding, and limited movements).

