#### Primary Outcome

ASDAS, including total back pain, patient global assessment of disease activity, peripheral pain or swelling, duration of morning stiffness, and C-reactive protein level, is the primary outcome [10].

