### Power Calculations

The sample size was calculated using ASDAS-CRP as the primary outcome. Based on a previous randomized controlled trial comparing supervised versus home-based exercise in patients with AS, the study of the effect size was 0.714 [6]. Assuming a 2-tailed independent *t* test with α=.05, power 1−β=.8, and a 1:1 allocation ratio, G*Power 3.1 estimated a required sample size of 32 participants per group (total N=64). To account for a conservative 20% attrition rate-consistent with dropout rates reported in comparable AS exercise trial, we increased the total sample size to N=80 (40 per group).

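### The primary comparison ignores baseline ASDAS-CRP, which is available for every participant; a baseline-adjusted ANCOVA would gain precision for one degree of freedom

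*Protocol article*

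**What the plan says.** The Statistical Analyses section gives one rule for all quantitative outcomes: "Statistical significance for quantitative variables is assessed using Student *t* test or 1-way ANOVA". The Abstract repeats it: "continuous variables will be compared with *t* tests or ANOVA". The Power Calculations section sizes the trial on the same kind of test: "Assuming a 2-tailed independent *t* test with α=.05", and of the effect it says "the study of the effect size was 0.714". None of these places mentions a covariate.

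The Abstract defines the endpoint: "The primary outcome is the change in Ankylosing Spondylitis Disease Activity Score with C-reactive protein (ASDAS-CRP) at 24 weeks". The Primary Outcome section lists the components of the score and ends "duration of morning stiffness, and C-reactive protein level, is the primary outcome", without repeating the word change or the time point.

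Baseline values exist for everyone, because the Participants section requires "stable drug treatment in the preceding month, and ASDAS-CRP between 1.3 and 3.5". Table 1 also schedules ASDAS-CRP at baseline and at 24 weeks, as it does most of the continuous secondary measures.

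**The concern.** When an outcome is measured before and after treatment, a model that includes the baseline value uses information that an unadjusted comparison discards. A t test on week-24 values ignores baseline altogether. A t test on change subtracts all of it, which is too much whenever the regression slope of follow-up on baseline is below 1. Both have a larger variance than ANCOVA unless the correlation is at an extreme: 0 for the week-24 value, 1 for change.

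Two things are at stake in a trial of 80. One is power and the width of the confidence interval. The other is that a chance baseline difference between arms passes into the unadjusted estimate, through regression to the mean for change and directly for the week-24 value.

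**Working it through.** **1. The plan's own figure.** Inputs from Power Calculations: d = 0.714, two-sided α = 0.05, power 0.80, 1:1 allocation, independent t test, 20% attrition. Noncentral-t power is 0.790 at 31 per arm and 0.803 at 32 per arm, so 32 is correct. Then 64 / 0.8 = 80. Both stated figures reproduce.

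**2. The analysis set.** The Missing Data section puts all randomised and consented patients in the full analysis set, with missing week-24 values filled by LOCF. The Results section gives 36 and 44. The planned comparison is therefore 36 against 44, not 64 evaluable patients.

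- Standard error factor: √(1/36 + 1/44) = 0.2247
- Noncentrality: 0.714 / 0.2247 = 3.177, with 78 df
- Unadjusted power: 0.881

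**3. Variance under ANCOVA.** Let ρ be the correlation between baseline and week-24 ASDAS-CRP, with equal variances assumed at the two times. In units of the variance of a single measurement, the week-24 value has variance 1, change has 2(1 − ρ), and the ANCOVA residual has 1 − ρ². The ratios are:

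- ANCOVA to week-24 value: 1 − ρ²
- ANCOVA to change: (1 − ρ²) / [2(1 − ρ)] = (1 + ρ)/2

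**4. Power at 36/44.** The effective d is 0.714 divided by the square root of the variance ratio. ANCOVA has N − 3 = 77 df. Its variance is inflated by 1 + 1/(N − 4) = 1 + 1/76 = 1.013 for estimating the slope. The article gives no ρ and does not say whether 0.714 refers to change or to the week-24 value, so both scales are shown over a range.

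| ρ (assumed) | Variance ratio to change | Power if d is on the change scale | Variance ratio to week-24 value | Power if d is on the week-24 scale |
|---|---|---|---|---|
| 0.3 | 0.65 | 0.97 | 0.91 | 0.90 |
| 0.5 | 0.75 | 0.95 | 0.75 | 0.95 |
| 0.7 | 0.85 | 0.92 | 0.51 | 0.99 |

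The unadjusted comparator is 0.88 in every row. The gain is 4 to 9 points on the change scale and 2 to 11 points on the week-24 scale.

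**5. Cost if baseline carries no information.** At ρ = 0 with d on the week-24 scale, power at 36/44 falls from 0.881 to 0.876.

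**6. Chance imbalance.** The standard error of the baseline difference is 0.2247 SD at 36/44, so P(|difference| > 0.3 SD) = P(|Z| > 0.3/0.2247) = 0.18. At 40/40 the standard error is √(2/40) = 0.2236 SD, and the probability is again 0.18. Given a 0.3 SD difference, the unadjusted estimate shifts by 0.3(1 − ρ) SD for change and 0.3ρ SD for the week-24 value. Over ρ = 0.3 to 0.7 that is 0.09 to 0.21 SD of a single measurement in either case.

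**The case against.** The strongest reply is that nothing here is an error. Under randomisation, a t test on change or on week-24 values is unbiased and holds its type I error, and the sample size was computed for the test that is planned. This stands, and it limits the point to efficiency and exposure to chance imbalance. A reader might infer that the planned primary analysis is invalid or the trial wrongly sized; the documents do not support that.

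Three further inferences are tempting and should not be drawn.

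- **That the 36 to 44 split signals baseline imbalance.** Unequal arm sizes say nothing about unequal baselines. The chance of a difference above 0.3 SD is 18% at 36/44 and at 40/40 alike.
- **That the endpoint is contradictory and leaves a free choice of scale.** The Abstract names change at 24 weeks. The Primary Outcome section is terse but states no competing endpoint, and the hypothesis in the Introduction speaks of improvement.
- **That the trial starts from 80% power on 64 patients, so that adjustment buys up to 13 or 14 points.** That does not match the planned full analysis set, where the unadjusted figure is 0.88.

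It is also fair to say that the gain rests on an unknown ρ. The entry window of 1.3 to 3.5 may lower ρ. On the week-24 scale a low ρ is where ANCOVA gains least; on the change scale it is where it gains most. The direction of the argument survives on both scales.

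An unseen analysis plan does not answer the point, because the article itself names the unadjusted test in three places.

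**Conclusion.** The point holds as a recommended improvement (should fix). The unadjusted test is valid and correctly sized, but it leaves usable information out of the primary comparison. At 36/44, ANCOVA would raise power from about 0.88 to between 0.92 and 0.97 if 0.714 is a change-scale effect, or to between 0.90 and 0.99 if it is a week-24 effect, for ρ from 0.3 to 0.7. It would also remove the effect of chance imbalance in baseline ASDAS-CRP, though not in covariates left out of the model.

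These figures assume equal variances at the two times and take d at face value. LOCF may dilute d. Table 1 schedules ASDAS-CRP only at baseline and week 24, so a dropout's carried-forward value would be the baseline one. The article gives no figure for the size of that dilution, and it would affect the adjusted and unadjusted analyses alike.

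**What to change.** Amend the analysis as follows:

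- Make the primary analysis an ANCOVA of week-24 ASDAS-CRP on arm, with baseline ASDAS-CRP as covariate. Report the adjusted difference with its 95% CI. Using change as the dependent variable in the same model gives the same arm effect and P value, so the Abstract's endpoint is respected.
- Use the same model, with the matching baseline, for each continuous secondary outcome that has one.
- State the primary endpoint in the same words in the Abstract and in the Primary Outcome section.
- Keep the t test as a supportive, unadjusted analysis.

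Timing matters. The article reports recruitment complete, its Abstract reports follow-up complete, and analysis is described as pending. The change therefore has to be a dated, documented amendment made before unblinded outcome data are analysed. Made later, it would itself look like a choice of result.

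No further data are needed, and the SPSS version already named can fit the model. The statistical cost is one degree of freedom.

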### Power Calculations

The sample size was calculated using ASDAS-CRP as the primary outcome. Based on a previous randomized controlled trial comparing supervised versus home-based exercise in patients with AS, the study of the effect size was 0.714 [6]. Assuming a 2-tailed independent *t* test with α=.05, power 1−β=.8, and a 1:1 allocation ratio, G*Power 3.1 estimated a required sample size of 32 participants per group (total N=64). To account for a conservative 20% attrition rate-consistent with dropout rates reported in comparable AS exercise trial, we increased the total sample size to N=80 (40 per group).

### Missing Data

Missing data due to participant dropout will be addressed using the Last Observation Carried Forward (LOCF) method for the primary analysis. Under this approach, missing values at the 24-week follow-up will be replaced with the last available measurement from earlier timepoints. This method assumes that unobserved outcomes remain stable after dropout, a rationale consistent with prior studies in chronic conditions like AS, where short-term interventions may yield sustained effects. All randomized and consented patients, constituting the full analysis set, are going to be included according to intention-to-treat principles for the efficacy analyses.

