### Assessments

For a schedule of data collection and measures list, refer to Table 1.

**Table 1 table1:** Measures and schedule for data collection.

Measure name			Screener		Baseline		24-week follow-up

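### No ASDAS-CRP assessment is scheduled between baseline and week 24, so the planned LOCF is baseline carried forward: each dropout counts as zero change, against the rule's own rationale and the sample-size assumption

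*Protocol article*

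**What the plan says.** The abstract (Methods) defines the endpoint: "The primary outcome is the change in Ankylosing Spondylitis Disease Activity Score with C-reactive protein (ASDAS-CRP) at 24 weeks".

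The Missing Data section names LOCF for the primary analysis and gives the rule: "missing values at the 24-week follow-up will be replaced with the last available measurement from earlier timepoints". It supports this by assuming that outcomes stay stable after dropout, as in chronic conditions "where short-term interventions may yield sustained effects". The same section puts all randomized, consented patients in the efficacy analysis.

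Table 1 in Assessments ("Measures and schedule for data collection") has three time columns: screener, baseline and 24-week follow-up. The ASDAS-CRP row is ticked at baseline and at 24 weeks only.

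Interventions mentions biweekly calls to control patients, for logbook data, adherence and questions, and a scheduled outpatient follow-up visit. No ASDAS-CRP measurement is attached to either.

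Power Calculations uses an effect size from an earlier trial ("the study of the effect size was 0.714") with "α=.05, power 1−β=.8, and a 1:1 allocation ratio" and a two-sided t test. It obtains 32 per group, then goes from 64 to 80: "To account for a conservative 20% attrition rate".

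**The concern.** LOCF is normally defended on the ground that the carried value was measured on treatment. On this schedule no such value exists for the primary outcome, so the rule becomes a different one: no dropout changed from baseline. The article does not say so, and the reason it gives, that effects are sustained, assumes the opposite of what the rule imposes.

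Two things are at stake. First, the primary estimate and P value depend on how many patients drop out of each arm. The Introduction says home-based exercise is itself beneficial, so improvement in both arms is plausible; zero change then penalizes the arm that loses more patients. Retention could well differ, since one arm has a sensor, app, automated reminders and weekly physiotherapist review, and the other a manual, paper logbook and biweekly calls. Second, the sample size treats dropouts as lost from the analysis at an undiluted effect, while the analysis keeps them in and dilutes the effect.

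**Working it through.** **1. The plan's own figure.** Inputs from Power Calculations: d = 0.714, two-sided α = 0.05, power 0.80, 1:1 allocation, 20% attrition. With the noncentral t distribution, 31 per arm gives power 0.790 and 32 per arm gives 0.803, so 32 per arm (64 in total) reproduces. Inflation: 64 / (1 − 0.20) = 80. Both steps are correct for 64 completers.

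**2. What the rule imputes.** Measured ASDAS-CRP values per patient: baseline and week 24. If week 24 is missing, the carried value is baseline, so the imputed change is baseline − baseline = 0.

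**3. Expected difference, equal dropout.** Take improvement as positive, completer SD = 1, control completers' mean improvement m, DFEP completers' mean m + 0.714, and a share q missing in each arm. The difference becomes

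(1 − q)(m + 0.714) − (1 − q)m = (1 − q) × 0.714.

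At q = 0.20: 0.8 × 0.714 = 0.571. This is a bias only if dropouts would have changed like completers.

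**4. Power, 40 per arm, all 80 analysed.**

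- SD left at 1: standardized difference 0.571, power 71.3% (70.9% at the actual 36/44 allocation). Reaching 80% would take 50 per arm.
- SD following the mixture of completers and zeros: arm variance = (1 − q) + q(1 − q)μ², with μ the arm's completer mean. For example, q = 0.20 and m = 0.5: DFEP variance 0.8 + 0.16 × 1.214² = 1.036, control variance 0.8 + 0.16 × 0.5² = 0.840, pooled SD 0.968, standardized difference 0.571 / 0.968 = 0.590, power 74.1%.

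| Control mean change m (assumed) | Power, 20% dropout | Power, 10% dropout |
|---|---|---|
| 0 SD | 78.6% | 84.0% |
| 0.5 SD | 74.1% | 81.9% |
| 1.0 SD | 66.6% | 78.1% |
| 1.5 SD | 57.7% | 72.8% |

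Simulation at 20% dropout (20,000 runs) gives 78.3%, 74.0% and 66.1% at m = 0, 0.5 and 1.0. With no dropout, power is 88.4% at 40/40 and 88.1% at 36/44, so the uneven allocation is not the issue.

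**5. Unequal dropout, illustration only.** With no true effect and a common improvement m, the expected difference is (q_control − q_DFEP) × m. For an assumed 10% DFEP / 30% control split this is 0.20 × 0.5 = 0.10 SD or 0.20 × 1.0 = 0.20 SD in favour of DFEP; reversing the split reverses the sign. Simulated two-sided type I error:

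| Common improvement (assumed) | 10%/30% split | 15%/25% split |
|---|---|---|
| 0 SD | about 5% | about 5% |
| 0.3 SD | about 6% | about 5% |
| 0.5 SD | about 8% | about 6% |
| 1.0 SD | about 15% | about 8% |

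With equal dropout, type I error stays at 5%.

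**The case against.** Several points on the other side stand.

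- A reader might infer that patients were not seen between baseline and week 24. The article does not say that: it mentions calls and an outpatient follow-up visit. What it lacks is a scheduled ASDAS-CRP measurement at either.
- A reader might infer that the primary effect is necessarily biased. It is not. If patients who stop exercising go back to baseline, zero change is right for them, and the article does not settle this. With equal dropout the rule only dilutes a superiority comparison, which is conservative.
- A reader might infer that the sample size is wrong or that 80% power is lost outright. The arithmetic is right for 64 completers. The loss depends on the control-arm change and on dropout by arm, and the readable text gives neither. It also gives no SD and does not say whether 0.714 refers to change or to week-24 scores. The 20% is described as conservative; at 10% dropout, power is about 78% to 84% for control changes of 1.0 to 0 SD.
- The larger type I errors need a wide dropout split together with substantial improvement in both arms. Figure 3, whose caption mentions withdrawals, is not visible here and may show the actual split.
- With no interim ASDAS-CRP value, multiple imputation from baseline covariates may add little to a baseline-adjusted complete-case analysis, and its missing-at-random assumption cannot be tested.

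None of this rescues the text as written. The section fixes the method, the analysis it applies to and the reason for it, so this is not detail left to an analysis plan, and the reason does not fit the rule.

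**Conclusion.** The point holds in conditional form and should be corrected before the analysis, because the rule governs the primary P value. It is certain from the article that, on the published schedule, LOCF for ASDAS-CRP is baseline carried forward, that the sustained-effects rationale has no on-treatment value to rest on, and that Power Calculations and Missing Data treat dropouts differently.

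The size is conditional. If dropouts would have changed like completers, 20% dropout in both arms reduces the estimate by a fifth. Power is then below 80% in every case computed, from a loss of about 1 point (controls do not change) to more than 20 points (controls improve by 1.5 SD). Inflation of type I error needs both unequal dropout and improvement in both arms; the splits and improvements used here are assumptions, not figures from the article.

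**What to change.** Before unblinded analysis:

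1. Replace LOCF in the primary analysis with ANCOVA of week-24 ASDAS-CRP on baseline ASDAS-CRP. Handle missing values under missing at random, by multiple imputation within arm from baseline covariates already collected or by the equivalent baseline-adjusted likelihood analysis.
2. Keep baseline carried forward as a sensitivity analysis under that name, preferably with a delta-adjusted analysis alongside it.
3. Delete the sustained-effects rationale from Missing Data.
4. If LOCF is kept as primary, call it baseline carried forward, state that it assumes no change in any dropout, and reconcile it with Power Calculations by giving power as a conditional range (at 20% dropout, about 71% with the SD unchanged and about 58% to 79% across the control changes above) rather than as one figure.

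The cost is a paragraph of analysis text and a few lines of code, with no new data; the article describes data analysis as still pending. The small downside is reliance on an untestable missing-at-random assumption, which the sensitivity analyses in step 2 address. Restating power cannot change a trial that has finished recruiting, but it tells readers how to weigh a null result.

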### Ethical Considerations

This study was approved by the Ethics Committee of the Chinese PLA General Hospital (number S2022-738-02) in compliance with the Declaration of Helsinki. All participants provided written consent after being informed of the study’s goals, procedures, risks, and benefits. They retained the right to withdraw at any time without affecting their care. Participant data were anonymized and securely stored on the Healbone platform using encryption, two-factor authentication, and restricted access. Personal details (eg, names) were stored separately. No financial payment was provided. Participants received standard clinical care and exercise programs for AS. No identifiable images or personal information appeared in this paper. Any future inclusion of such content will require explicit written consent.

## Results

The recruitment of the first participant began on February 27, 2023. We have screened 216 outpatients who may be eligible subjects, among them 126 outpatients who initially met the inclusion criteria. After evaluating clinicians performed face-to-face assessments, 23 lacked a stable medication regimen, 5 presented with severe cervical vertebral bridges, 3 reported regular structured exercise, 2 could not be reached after prescreening, 10 had significant cardiovascular disease, and 3 declined participation due to time constraints. Ultimately, 80 eligible participants were enrolled, with 36 randomly allocated to the intervention group and 44 to the control group (Figure 1). Recruitment was completed on March 5, 2024, and the final participant was expected to complete the study in September 2024. Data analysis (November 2024) and result dissemination (April 2025) are pending.

